## Abstract

**Background:**

Irreversible pulpitis is a highly painful inflammatory condition of the dental pulp which represents a common dental emergency. Recommended care is partial endodontic treatment. The dental literature reports major difficulties in achieving adequate analgesia to perform this emergency treatment, especially in the case of mandibular molars. In current practice, short-course, orally administered corticotherapy is used for the management of oral pain of inflammatory origin. The efficacy of intraosseous local steroid injections for irreversible pulpitis in mandibular molars has already been demonstrated but resulted in local comorbidities. Oral administration of short-course prednisolone is simple and safe but its efficacy to manage pain caused by irreversible pulpitis has not yet been demonstrated. This trial aims to evaluate the noninferiority of short-course, orally administered corticotherapy versus partial endodontic treatment for the emergency care of irreversible pulpitis in mandibular molars.

**Methods/design:**

This study is a noninferiority, open-label, randomized controlled clinical trial conducted at the Bordeaux University Hospital. One hundred and twenty subjects will be randomized in two 1:1 parallel arms: the intervention arm will receive one oral dose of prednisolone (1 mg/kg) during the emergency visit, followed by one morning dose each day for 3 days and the reference arm will receive partial endodontic treatment. Both groups will receive planned complete endodontic treatment 72 h after enrollment. The primary outcome is the proportion of patients with pain intensity below 5 on a Numeric Scale 24 h after the emergency visit. Secondary outcomes include comfort during care, the number of injected anesthetic cartridges when performing complete endodontic treatment, the number of antalgic drugs and the number of patients coming back for consultation after 72 h.

**Discussion:**

This randomized trial will assess the ability of short-term corticotherapy to reduce pain in irreversible pulpitis as a simple and rapid alternative to partial endodontic treatment and to enable planning of endodontic treatment in optimal analgesic conditions.

**Trial registration:**

ClinicalTrials.gov, identifier: NCT02629042. Registered on 7 December 2015.

(Version n°1.1 28 July 2015)

**Electronic supplementary material:**

The online version of this article (doi:10.1186/s13063-017-1883-x) contains supplementary material, which is available to authorized users.

## Background

Irreversible pulpitis is an inflammatory condition of the dental pulp, highly painful, and one of the main reasons for seeking emergency dental treatment [1, 2]. Pain associated with irreversible pulpitis represents more than 45% of the reasons for dental emergency consultation in hospital [3]. Diagnosis of symptomatic irreversible pulpitis is based on clinical findings such as spontaneous mild to severe pain that remains after removal of the stimulus. The most widely used clinical test is the response to heat or cold sensitivity test. The main etiology of irreversible pulpitis is an infectious lesion due to decay or loss of seal under restorations. After tooth trauma, pulp exposure or cracks can also induce a pulpal inflammatory response [4]. Recommended emergency care is partial endodontic treatment under local and/or locoregional anesthesia [5, 6]. The purpose of emergency partial endodontic treatment is to stop the pain of pulpitis by removing a portion of the pulp [7]. Compared to complete pulpectomy, the pulpotomy procedure results in a lower incidence of post-treatment pain [8, 9]. Several dressings can be used after emergency pulpotomies, camphorated phenol, eugenol, isotonic saline and cresatin, without contribution for the relief of pain [7]. Ideally, complete final endodontic treatment is performed in the following 72 h, as 55% of patients experience moderate to severe pain due to pulpotomy [10, 11]. The dental literature reports major difficulty in achieving adequate anesthesia in the mandible in order to perform partial endodontic treatment, especially for molars [12, 13]. This results in a very painful care experience for the patient [14]. Management of this type of emergency is costly for health facilities in terms of equipment and time as pulpotomy is the only emergency treatment recommended [14]. Patient comfort, cost-saving and rationalization of care time justify the search for an alternative to emergency partial endodontic treatment. A recent systematic review by Shirvani et al. [15] showed superior intraoperative analgesia for patients with irreversible pulpitis after administration of preemptive nonsteroidal anti-inflammatory drugs. But, to our knowledge, no clinical trial on the use of orally administered corticosteroid for the treatment of dental pulp inflammation has been conducted. In current practice, short-course, orally administered corticotherapy (prednisolone) is used to manage oral pain of inflammatory origin [16–18]. Glucocorticoids, thanks to their anti-inflammatory action, can neutralize the inflammatory mediators [19]. Pulp inflammation can be treated using this molecule: the efficacy of intraosseous local steroid injection for irreversible pulpitis of mandibular molars has already been demonstrated, but this results in local comorbidities and requires specific materials [20, 21]. Oral administration of short-course prednisolone is simple and safe but its efficacy to manage pain caused by irreversible pulpitis has not yet been demonstrated. Administration of prednisolone per os has a very high (90%) and rapid (at least 4 h) bioavailability. No difference in efficacy between intravenous and oral administration of this molecule was reported in the case of multiple sclerosis [22]. This oral treatment could limit comorbidities and technical difficulties associated with intraosseous injection and could make it possible for complete endodontic treatment to be delayed to 72 h later in optimal conditions of analgesia for the patient. Despite the difficulties described concerning partial endodontic treatment, it is very effective in terms of pain reduction and can achieve a success rate of 100%. A noninferiority design was, therefore, chosen to compare the effect of short-course, orally administered corticotherapy with partial endodontic treatment in terms of pain reduction during adult emergency care for irreversible pulpitis in permanent mandibular molars.

### Objectives

The primary objective of the trial is to compare the effect on pain of short-course, orally administered corticotherapy versus partial endodontic treatment during adult emergency care for irreversible pulpitis in permanent mandibular molars, 24 h after the emergency visit.

The hypothesis is that short-course, orally administered corticotherapy is noninferior to partial endodontic treatment in terms of analgesic efficacy but superior in terms of number of antalgic drugs taken, number of patients coming back to consultation 72 h later, patient comfort and number of injected anesthetic cartridges when performing endodontic treatment.

The secondary objective consists in comparing, depending on the treatment strategy:Patient’s comfort during endodontic treatment measured using the “Iowa Satisfaction with Anesthesia Scale” (ISAS) [23]Number of analgesic drugs (step 1 on the World Health Organization analgesic ladder or step 2, taken after the inclusion visit and over 72 h)Difference in pain measured using the Numeric Scale (NS) between the emergency visit and 24 h thereafterKinetics of pain, self-assessed using the NS at 6, 12, 24, 48 and 72 h after the emergency visitNumber of injected anesthetic cartridges to achieve absence of pain during complete endodontic treatmentNumber of patients returning for complete endodontic treatment

## Methods/design

The trial protocol was developed in accordance with the Consolidated Standards of Reporting Trials (CONSORT) Statement extension for “Non-Inferiority and Equivalence Trials” [24].

The trial design and protocol adhere to Standard Protocol Items: Recommendations for Interventional Trials (SPIRIT) criteria; the SPIRIT Checklist can be found as Additional file 1: Table S1.

### Design

A noninferiority, open-label, randomized controlled clinical trial will be conducted in two dental subunits of the Bordeaux University Hospital. Eligible patients will be recruited during their emergency visit when presenting irreversible pulpitis in the first or second mandibular molars. Diagnosis will be based on clinical and radiographic examination. Two parallel groups will be randomized so that patients will receive: (1) partial endodontic treatment (reference) or (2) short-course, orally administered corticotherapy (intervention to evaluate) (Fig. 1).

**Fig. 1 Fig1:**
[figure not shown]
Flowchart of a trial evaluating the noninferiority of short-course, orally administered corticotherapy versus partial endodontic treatment for the pain management in the emergency care of irreversible pulpitis in mandibular molars at the Bordeaux University Hospital

#### Participants

Adult patients seeking emergency consultation at the dental department of the teaching hospital in Bordeaux (France) will be recruited if they meet the eligibility criteria. Pulpitis on third molars will be discarded in order to exclude any bias linked to technical difficulties generated by restriction of mouth-opening.

Participants will be included if they meet the following inclusion criteria:Clinical signs of irreversible pulpitis of the first or second mandibular molarASA1 or ASA2 score (American Society of Anesthesiologists)Aged between 18 and 70 years (of either gender)Able to give written informed consentAffiliated with a health insurance schemeAgree to be contacted by phone 24 h after the emergency visitAvailable to come back 72 h after the emergency visit for complete endodontic treatment

Participants will not be included if they present at least one of the following noninclusion criteria:Diagnosis of irreversible pulpitis of the third mandibular molar, reversible pulpitis, acute apical periodontitis, periodontal lesion of endodontic origin or dentin syndromeNonretainable tooth requiring extractionContraindication for endodontic treatment (endocarditis risk), contraindication for the prescription of glucocorticoids or codeineViral disease in evolution (hepatitis, herpes zoster, etc.), machine operators due to the risk of somnolence and lack of attention induced by drugsPsychosis uncontrolled by treatment, allergy to one or more of the componentsImmunization with live vaccineDiabetes, drug intake with direct interaction with glucocorticoids or codeine, woman of child-bearing age without contraception, pregnant, breastfeedingNot able to give informed consentParticipating in another interventional study

#### Outcomes

The primary outcome is the proportion of patients with pain intensity of below 5 on a Numerical Scale (NS <5) 24 h after the emergency visit [25]. The NS has already been used for the assessment of pain in previous studies to evaluate the efficacy of orally administered corticosteroids on pharyngitis presenting as an emergency [26]. Briefly, the patient will be asked to make a pain rating according to a NS score ranging from 0 to 10. A clinical research assistant will directly phone the patient and will use a standardized sentence: «Please indicate the intensity of your pain level on a scale of 0 (no pain) to 10 (worst pain imaginable)».

Secondary outcomes include:Number of analgesic drugs (step 1 on the World Health Organization analgesic ladder (paracetamol 1 g) or step 2 (paracetamol 600 mg/codeine 50 mg) taken after the inclusion visit up to 72 h)Difference in pain measured using the NS between T0 (baseline) and 24 h after the emergency visit (T1)Kinetics of pain, self-assessed using the NS at 6, 12, 24, 48 and 72 h after T0Patient’s comfort during complete endodontic treatment measured using the “Iowa Satisfaction with Anesthesia Scale” (ISAS) [23]Number of injected anesthetic cartridges required to achieve clinical silence for the realization of complete endodontic treatmentNumber of patients returning for the T2 visit

### Study timelines

All patients seeking emergency consultation at the dental subunits of the Bordeaux University Hospital will be screened for the selection criteria.

If a patient meets all criteria, they will be informed by an investigator of the study, who will tell them about the objectives, methods, follow-up, risks and restrictions. They will be given an Information Sheet and an Informed Consent Form so that they can read them and ask any questions. If the patient agrees, they will sign the Informed Consent Form and will be included in the study (T0).

The investigator in charge of the emergency room will proceed to randomization (see below) and another investigator will conduct the T0 (baseline) visit according to the affected group to which the patient will be allocated. The patient will be contacted directly by a research assistant, blinded to the affected group, 24 h after inclusion to gather the information on pain intensity 24 h after the emergency visit (T1). The patient will then receive complete endodontic treatment 72 h after T0 (T2) (Fig. 2).

**Fig. 2 Fig2:**
[figure not shown]
Schedule of enrollment, interventions and assessments during PULPISOLONE

#### Interventions

The evaluated intervention consists of oral administration of prednisolone (1 mg/kg) during the emergency visit, followed by one morning dose each day for 3 days.

Reference management consists of local and locoregional anesthesia of the molar and partial endodontic treatment. Partial endodontic treatment is a pulpotomy. After preparation and removal of any carious tissue, the tooth will be isolated with a rubber dam and pulpal parenchyma will be removed. Pulpal bleeding will be controlled using 2.5% sodium hypochlorite and the site will be covered with calcium hydroxide and a temporary filling.

At the end of T0, all the patients, whatever their randomization group, will be given two types of antalgics and given the recommendation to take them only if they experience pain. Specifically, it will be recommended to take either a step-1 antalgic (paracetamol 1 g) or a step-2 antalgic (paracetamol 600 mg/codeine 50 mg) every 6 h in case of moderate or severe pain, respectively.

At T2, all patients, will receive full endodontic treatment following local and locoregional anesthesia.

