### Statistical analysis

The main analysis will be intention-to-treat (ITT) using the «missing = failure» strategy. A robustness analysis, supported by the per-protocol approach, will be carried out.

The difference between the two arms in the number of patients with pain <5 on the NS will be measured using its unilateral 97.5% confidence interval (CI) according to the binomial exact formula. The noninferiority hypothesis will be accepted if the lower confidence limit is superior to the noninferiority margin, which is fixed as −20%.

For qualitative outcomes, frequencies between the two groups will be compared using the chi-square test, or Yates’s corrected chi-square or Fisher’s exact tests, depending on the variables’ distributions. For quantitative outcomes, means will be compared using Student or Wilcoxon tests according to variables’ distributions. Regression model will be used to adjust on major confounding factors (i.e., age and sex). The statistical significance threshold will be 0.05.

Basic statistics in the study report will include information on missing values for all relevant study variables. A summary of baseline patient characteristics with totals and proportions (%) for categorical variables, and minimum, maximum, interquartile ranges and standard deviations for continuous variables will be presented. An estimation of primary and secondary outcomes will be calculated using their 95% CI.

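### The 24 h success count takes no account of the on-demand analgesics supplied to both arms, so on its own it supports a comparison of strategies, not of the corticotherapy's own analgesic effect

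*Protocol article*

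**What the plan says.** All references are to the protocol article.

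- **Outcomes.** Success in the primary comparison is defined by "the proportion of patients with pain intensity of below 5 on a Numerical Scale (NS <5) 24 h after the emergency visit". No condition on analgesic intake is attached. Determination of sample size defines success in the same way.
- **Interventions.** Patients in both arms "will be given two types of antalgics and given the recommendation to take them only if they experience pain". The step-1 drug is meant for moderate pain and the step-2 drug, paracetamol with codeine, for severe pain, each repeatable at 6 h intervals. Both drugs are thus to hand throughout the 24 h before the primary rating.
- **Study timelines.** The blinded research assistant calls "to gather the information on pain intensity 24 h after the emergency visit (T1"). The text names no other item for this call.
- **Outcomes, secondary.** The number of step-1 and step-2 analgesics is counted when "taken after the inclusion visit up to 72 h", that is, over three times the primary window.
- **Statistical analysis.** "The main analysis will be intention-to-treat (ITT) using the «missing = failure» strategy", with a per-protocol robustness analysis. "The noninferiority hypothesis will be accepted if the lower confidence limit is superior to the noninferiority margin", fixed at −20%. Nothing in the rule refers to analgesic use.
- **Objectives.** The hypothesis is that corticotherapy is noninferior in analgesic efficacy and superior on several secondary outcomes, including the number of analgesic drugs taken.

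**The concern.** Take a patient whose assigned treatment has not controlled the pain, who takes the step-2 drug as advised and who rates 3 when called. That patient counts as a success of the assigned treatment. Equal access in both arms does not cancel this, because the drugs are taken in response to pain and the less effective arm has more failures to convert. The two observed success rates move towards each other.

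In a superiority trial that movement would work against the claim. Here it works for it. Neither planned analysis set deals with it: the missing-equals-failure rule concerns absent ratings, and taking the supplied analgesics is compliant, so it gives no reason for exclusion from the per-protocol set. What is at stake is how the conclusion may be worded. A favourable result could be read as showing that prednisolone controls the pain about as well as pulpotomy, when part of the control came from paracetamol and codeine.

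**Working it through.** **Inputs from the protocol article.** Reference success 95%, margin 20 points, one-sided alpha 0.025, 60 per group, 5% loss (Determination of sample size). Newcombe's method was used for planning. The Statistical analysis section names a binomial exact formula instead. Newcombe is used below, and the direction of the result does not depend on that choice.

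**Input assumed.** f is the share of would-be failures in each arm that the analgesics bring below 5 at the call. The document gives no figure for it. The range shown is 0 to 50%, equal in both arms.

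**Step 1: the plan's own figures.** Both binomials are enumerated exactly, using the Wilson-based Newcombe lower limit without continuity correction.
- 40 per group, 95% in both arms: power 92.8%, consistent with the stated 90%.
- 60 × 0.95 = 57 evaluable per group: power 93.5% at 93% vs 95% and 89.0% at 92% vs 95%. Both stated minimums (90% and 80%) hold.

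**Step 2: effect of the analgesics on the difference.** The observed rate in an arm is p + f(1 − p). The observed difference is therefore (1 − f) times the difference without analgesics. For 75% vs 95%:
- f = 10%: 0.75 + 0.10 × 0.25 = 77.5%, against 0.95 + 0.10 × 0.05 = 95.5%; difference −18 points.
- f = 25%: 81.25% vs 96.25%; difference −15 points.
- f = 50%: 87.5% vs 97.5%; difference −10 points.

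**Step 3: chance of declaring noninferiority**, 60 per arm, lower limit above −20%:

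| Rates without analgesics | f = 0 | f = 10% | f = 25% | f = 50% |
|---|---|---|---|---|
| 75% vs 95% (at the margin) | 2.5% | 4.9% | 12.6% | 43.3% |
| 70% vs 95% | 0.3% | 0.9% | 3.8% | 24.8% |

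**Step 4: what a rescue-adjusted success definition does to power.** Counting analgesic use as failure removes the dependence on f, but success rates fall below the planned 95%. With equal true rates in both arms and 57 evaluable per arm, power is 98.5% at 95% success, 91.6% at 90%, 83.7% at 85% and 71.2% at 75%. With the plan's own 2-point deficit it is 93.4%, 82.8%, 73.8% and 61.4%.

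**The case against.** The strongest reply is that the trial's error rate is not inflated at all on its own endpoint. The 95% and the 20-point margin are both stated for a score below 5 at 24 h, in a trial where everyone holds the same analgesics. On that scale the error at the margin stays at about 2.5%. Comparing two emergency strategies, each with on-demand analgesia, is a legitimate question, and the lead-in to the secondary objectives does speak of treatment strategy. A reader might infer from the table that the trial will produce a false noninferiority verdict. The document does not support that: the higher percentages arise only when the margin is applied to rates without analgesics, and only for assumed values of f.

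Nor is analgesic use ignored altogether. It is a named secondary outcome on which prednisolone is expected to be superior, and pain is also scored at 6, 12, 24, 48 and 72 h. Heavy rescue in the prednisolone arm would be visible. What remains is that the count runs to 72 h and has no bearing on the verdict.

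A supportive analysis could also sit in an analysis plan that is not shown, and the schedule figure is not shown, so what else is recorded by 24 h cannot be judged. But the primary outcome, the decision rule and the wording of the hypothesis are fixed in this document, and the mismatch lies between those three.

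Finally, a composite is not neutral. Patients know their arm, and that knowledge may affect whether they take an analgesic. The Background reports moderate to severe pain in 55% after pulpotomy, so composite failures could even concentrate in the reference arm. This stands as a reason not to let the composite decide the trial.

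**Conclusion.** The point holds as a mismatch between the primary endpoint and the claim to be drawn from it. As defined, the 24 h result can support noninferiority of prednisolone with on-demand analgesics against pulpotomy with the same. Alone, it does not establish that corticotherapy itself has noninferior analgesic efficacy, which is how the Objectives section words the hypothesis.

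The direction is clear if the analgesics relieve a similar share of failures in each arm: the difference shrinks by the factor 1 − f, towards the claim. The size is not known. At the margin it ranges from about 5% at f = 10% to about 43% at f = 50%, against 2.5% with no masking. For 70% vs 95% it ranges from about 1% to about 25%. The sample size reproduces and is not in question for the outcome as defined.

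**What to change.** 1. At the existing 24 h call, after the pain question, record the type, number and time of analgesics taken since T0.
2. Pre-specify a supportive analysis with the same interval and the same −20% margin, in which success is a score below 5 and no step-2 analgesic in the preceding 6 h (the dosing interval the protocol itself gives). Add a variant that counts any analgesic use up to 24 h as failure.
3. Report analgesic use to 24 h by arm beside the primary result.
4. Word the conclusion as noninferiority of the strategy with on-demand analgesics unless the supportive analyses agree with the primary one.

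The primary outcome stays as it is, the composite is not made a formal co-primary hurdle, and no change to the analgesic provision is proposed.

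**Cost.** One more question on a call already made, and extra analyses. The supportive analyses will have lower success rates and less power: about 92%, 84% and 71% at equal success of 90%, 85% and 75% with 57 evaluable per arm. Failure to agree may therefore reflect imprecision and should be reported as such. The open-label influence on the decision to take analgesics remains a limitation. The recording must be in place before enrolment, because the timing of intake before the call cannot be reliably recovered later.
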